## Abstract

**Background:**

Peripheral arterial disease (PAD) and local infections increase the risk of non-healing diabetic foot ulcers (DFU) and limb amputations but are treatable by percutaneous transluminal angioplasty (PTA), local wound care and antibiotic therapy. The exact time to treat chronic leg artery stenosis (LAS) and the role of microbiome composition in DFU remain unclear. This study aims to assess whether an early PTA within 48 h after diagnosing a LAS offers advantages over standard care.

**Methods:**

The PTA-DFS Study is a randomised controlled monocentric trial including individuals with T2D and DFU, aged > 18 years with haemodynamically relevant chronic LAS. The primary study endpoint is to investigate the impact of the early PTA within 48 h on wound-healing assessed by wound area changes after PTA using a 3D-camera with artificial intelligence (AI)-based wound-analysis-system. The secondary endpoint is the effect of early PTA on the combined occurrence of major adverse limb (MALE) and safety-related cardiac events (MACE) over 12 month post-angioplasty using time-to-event analysis. Additional secondary outcomes are time to complete wound healing, major amputation rate and the need for new revascularization. Explanatory variables for wound healing are wound microbiome changes using whole-genome sequencing and oxygen saturation of the wound environment measured using near-infrared spectroscopy. Data will be collected at baseline, 24 h, 1, 2, 3, 6, and 12 months after PTA. Diabetic kidney disease, distal symmetric polyneuropathy, retinopathy, cardiomyopathy, LAS will be assessed by laboratory analyses, clinical scores, AI-based fundus photography, echocardiography, duplex sonography, and pulse oscillography.

**Discussion:**

The PTA-DFS aims to improve diagnostic and therapeutic algorithms, risk assessment and enable tailored therapies for persons with T2D and ischemic DFU.

**Trial registration:**

Trial Registration Number: NCT06124586 (Registration Date: 2023–08-2).

## Background

Diabetic foot syndrome (DFS) refers to a spectrum of foot pathologies in persons with diabetes, including microvascular and macrovascular disorders. Factors such as distal symmetric polyneuropathy (DSPN), peripheral artery disease (PAD), and immune system impairment increase the risk of soft tissue injuries and infections in diabetic foot ulcers (DFU) [1]. Infected DFU are the leading cause of diabetes-related hospital admissions [2]. The lifetime risk of developing a DFU is reported to be 19–34%, with infections occurring in 50–60% of ulcers [3]. Approximately 20% of diabetic foot infections (DFI) result in lower-extremity amputations, accounting for 44% of minor and 18% of major amputations [4]. Osteomyelitis occurs in 44–68% of hospitalised persons with DFI and is the leading cause of amputation [5].

PAD, characterised by lower-limb artery stenosis, is a critical complication of type 2 diabetes (T2D) and affects more than 50% of persons with DFS, significantly increasing the risk of amputation [6]. Similarly, microcirculatory disorders are major contributors to non-healing foot ulcers [7]. Independent of traditional risk factors, the presence of microvascular disease alone increases the risk of amputation and synergistically increases the risk in persons with PAD [8]. DSPN and impaired microcirculation are closely interrelated, as nerve damage can impair blood flow regulation, leading to further ischemia and exacerbating microvascular dysfunction. Conversely, poor microcirculation can worsen nerve damage, perpetuating a cycle that accelerates the progression of both conditions. Current peripheral blood perfusion measurements (e.g., ankle-brachial index (ABI) or duplex sonography) do not capture microcirculatory disorders, especially in the context of diabetes-induced medial arterial calcification. Peripheral tissue perfusion in DFS is clinically often underestimated due to the warm and painless presentation in peripheral polyneuropathy, potentially delaying crucial vascular treatments like percutaneous transluminal angioplasty (PTA) [9]. Minimally invasive endovascular therapy, such as PTA, is beneficial for high-risk individuals with ischemic and neuropathic DFUs, offering limb preservation rates as high as 94% [10–12]. However, amputation rates remain high in this group, and there is a lack of randomised controlled trials (RCTs) investigating the effects of early PTA in persons with PAD and DFU. It remains unclear whether early revascularisation (within 48 h) after PAD diagnosis, particularly in persons with microangiopathy, can improve outcomes.

The wound microbiome could play a key role in DFU outcomes, with microbial dysbiosis driving infection, worsening ulceration and ultimately resulting in major amputations or sepsis [13]. The beta-diversity of microbial samples can indicate differences in bacterial populations between patient samples or body sites, helping to understand variations in disease development or treatment responses [14]. Thus, the effect of PTA on changes in beta-diversity of the wound microbiome is yet not well understood [12, 15]. The microbiome composition as assessed by novel molecular (metagenomic) microbiological assessment may influence chronic infection and wound healing [16]. Current guidelines of the International Working Group on the Diabetic Foot (IWGDF) call for studies that provide new insights into these interactions [17]. PTA may alter the wound environment by enhancing oxygenation, potentially influencing the microbiome. However, restored blood flow might also lead to systemic changes, such as increased cytokine release or microbial translocation into the bloodstream [18, 19]. The role of molecular microbiological testing in guiding antimicrobial therapy and enhancing DFU outcomes requires further investigation [17]. Cell-free microbial DNA, released from infected tissues, is gaining attention as a potential biomarker for infection monitoring post-PTA [18, 19]. Results from this monocentric RCT study could guide the rational use of antibiotics and improve infection control following endovascular interventions in DFU persons. Biomarkers, such as endothelial proteins and apoptotic markers, may help diagnose ischemic DFU and predict outcomes, although their clinical utility remains unclear [20–22].

This RCT will assess whether PTA within 48 h improves wound healing and reduces complications in participants with chronic ischemic DFUs over a 12-month period compared to standard care. The primary endpoint is the effect of early PTA on wound healing. Secondary endpoints include the combined occurrence of major adverse limb events (MALE), which serve as limb-specific outcomes, and major adverse cardiac events (MACE), which are considered safety-related secondary outcomes. Additional secondary endpoints include time to complete wound healing, major (above-ankle) amputation rate, and the need for new revascularization. Explanatory objectives are changes in wound microbiome composition and local microcirculation. The findings will inform the timing of PTA in managing DFS and help tailor more personalised and effective interventions for T2D persons. The study will also explore whether the baseline wound microbiome can predict healing outcomes.

## Methods/design

### Study design and randomisation protocol

The PTA-DFS Study is a prospective, monocentric, RCT including participants with T2D and ischemic DFU. Ethics approval was obtained from the local ethics committee (Heinrich Heine University, Düsseldorf, Germany) in accordance with the Declaration of Helsinki (#2022–2291). The PTA-DFS study is registered at www.clinicaltrials.gov (NCT06124586; Registration Date: 2023–08-2).

Participants will be randomly assigned in a 1:1 ratio to either the early PTA group (‘immediate PTA‘ within 48 h after leg artery stenosis (LAS) diagnosis or the elective PTA group (standard of care with PTA within 6 weeks) at the academic hospital of the Heinrich Heine University Düsseldorf, Germany, with inclusion of 200 participants within 5 years. All study participants included in the study will provide informed consent. Although the study is unblinded for both participants and physicians due to practical feasibility, blinding will be applied during the data analysis phase, with separate analysis of primary and secondary endpoints by interventionists (physicians or clinicians) and data analysts to minimise bias. After the data is unblinded, all results will be reviewed collectively. This approach aims to ensure more accurate and unbiased analysis of the primary and secondary endpoints.

Randomisation is performed using a computer-generated sequence with block randomisation to ensure unbiased allocation. The block size will be specified in advance, using blocks of 4 or 6, to maintain balance across groups throughout the study. Both groups receive standard care, with the only difference being the timing of the PTA procedure. The study is structured to ensure that, apart from the timing of PTA, all other aspects of care are consistent across both groups. All subsequent laboratory analyses will be performed in a blinded manner, without knowledge of randomisation. Aside from the timing of PTA, baseline and follow-up examinations will be conducted uniformly across both groups. To optimise recruitment efficiency, training sessions will be held with the interventional angiology staff and the diabetic foot care team, ensuring participants and staff are fully informed about study-related procedures and analyses during their state-of-the-art clinical care.

As illustrated in the study flow (Fig. 1), data will be collected at baseline recruitment (V0), during the index hospitalisation (V1; PTA and 24 h thereafter), and at follow-up visits at 1 (V2), 2 (V3), 3 (V4), 6 (V5), and 12 months (V6) post-PTA. If complications in wound healing occur in the elective group, crossover to the ‘immediate‘ PTA group will be implemented. Each patient will receive guideline-directed therapy for DFU, monitored and documented by specialised staff during clinical follow-ups and all study visits. Table 1 outlines the key analyses and corresponding time points throughout the study.

**Table 1 Tab1:** Study protocol. Table showing most relevant analyses and respective time points during the study period

Action								
**Visit (V)**	**Baseline**	**PTA**	**Follow-ups**					
	**V0**		**V1**	**V2**	**V3**	**V4**	**V5**	**V 6**
Time Point	0	0	0	1	2	3	6	12
Enrolment								
Eligibility Screen	X							
Informed Consent	X							
Randomisation	X							
Pseudonymisation	X							
Intervention		X						
Assessments								
Doppler/Duplex ultrasound	X		X	X	X	X	X	X
Segmental pulse oscillography	X		X	X	X	X	X	X
DSNP Screening (NDS, NSS)	X							
AI-based wound area documentation	X		X	X	X	X	X	X
Wound tissue oxygenation (NIRS)	X		X	X	X	X	X	X
AI-based retinal imaging	X							
TTE	X							
Fasting blood Sampling & Biobanking	X		X	X	X	X	X	X
Wound Swabbing & Biobanking	X		X	X	X	X	X	X
Wound Sampling & Biobanking	X		X	X	X	X	X	X
Urine Measurement	X							
Questionnaires	X		X	X	X	X	X	X
Outcome Assessment								
Primary Endpoint (wound healing)			X	X	X	X	X	X
Secondary Endpoint (MACE/MALE)			X	X	X	X	X	X

*DSPN* Distal symmetric polyneuropathy, *NDS* Neuropathy Disability Score, *NSS* Neuropathy Symptom Score, *AI* Artificial intelligence, *NIRS* Near-Infrared Spectroscopy, *TTE* Transthoracic Echocardiogram, *PTA* Percutaneous transluminal angioplasty, *MALE* Major adverse limb events, *MACE* Major adverse cardiac events

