### Statistical methods and power calculation

The primary endpoint focuses on the difference in changes of wound area (delta wound area at first - last visit) in T2D participants after early PTA compared to individuals with standard PTA. For the primary—change in wound area after early PTA—and secondary endpoint—combined incidence of MALE and MACE—a power calculation was performed. Assuming a medium effect size (Cohen's d = 0.4), corresponding to 0.4 standard deviations of the difference in delta wound area and difference in time-to-event from baseline to last visit between groups, a sample size of n = 100 per group (total n = 200) is required to achieve 80% power at alpha = 0.05.

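### The crossover rule moves poorly healing elective patients into the immediate PTA group and the primary comparison is worded by PTA received; read literally, group membership depends on a correlate of the primary outcome

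*Protocol article*

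**What the plan says.** All references are to the protocol article.

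- **Allocation** (Study design and randomisation protocol): "Participants will be randomly assigned in a 1:1 ratio". The early arm, also called the immediate PTA group, is treated "within 48 h after leg artery stenosis (LAS) diagnosis". The comparator is "the elective PTA group (standard of care with PTA within 6 weeks" of diagnosis or enrolment; the article does not say which.
- **Crossover** (same section, with the visit schedule): "If complications in wound healing occur in the elective group, crossover to the" immediate "PTA group will be implemented". The rule runs one way only, and no criterion for a complication is given.
- **Blinding** (same section): "the study is unblinded for both participants and physicians due to practical feasibility", so those who would apply the rule know the allocation.
- **Primary comparison** (Statistical methods and power calculation): the variable is the change in wound area from first to last visit. The people compared are described by the PTA they had: "in T2D participants after early PTA compared to individuals with standard PTA". The planned effect is d = 0.4, with 100 per group for 80% power.
- **Wording that points the other way**: the microbiome mixed models use treatment group, the imputation model uses treatment arm, and the power statement speaks of differences between groups.
- **Sensitivity analyses**: those listed all concern missing data. None deals with crossover.

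**The concern.** Three statements do not fit together. The early arm is defined by PTA within 48 h of diagnosis. The crossover sentence puts into that arm patients who develop a complication while waiting, most of whom would be past 48 h. The primary comparison is then phrased by which PTA a participant had.

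An analyst who follows the text as written would take elective patients with poor early healing out of their randomised arm and count them as early PTA. Early healing is related to the change in wound area at the last visit, so the worse outcomes would pass from one side of the comparison to the other. The comparison would no longer be protected by randomisation, and a real benefit of early PTA could be hidden or even appear reversed. Dropping these patients from the analysis would also distort the comparison, though less.

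**Working it through.** **1. The plan's own figure.** For d = 0.4, two-sided alpha 0.05 and 80% power, n per group = 2(1.960 + 0.842)² / 0.4² = 98.1, so 99. The article states 100, which gives power of about 0.81. The sample size is right on its own inputs, and it carries no visible allowance for crossover.

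**2. Set-up for the literal reading.** Take a unit-SD outcome, change from V0, with positive values meaning more healing. The early mean is D and the elective mean is 0. The worst fraction q of elective patients, ranked on an early-healing signal with correlation ρ to the final change, is moved. They gain a share g of D from their earlier PTA. The values of q, ρ and g are assumptions. Only D = 0.40 comes from the article.

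With φ the normal density at the q-quantile:
- moved patients have mean −ρφ/q + gD
- remaining elective patients have mean ρφ/(1 − q)
- counted as early PTA: d = (D − ρφ + gDq)/(1 + q) − ρφ/(1 − q)
- excluded: d = D − ρφ/(1 − q)
- by randomised arm: d = D(1 − gq)

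**3. The ends of the range, D = 0.40.**
- Mildest (q = 0.05, φ = 0.1031, ρ = 0.3, g = 1). Moved: (0.40 − 0.031 + 0.020)/1.05 − 0.031/0.95 = 0.34. Excluded: 0.40 − 0.033 = 0.37.
- Strongest (q = 0.20, φ = 0.2800, ρ = 0.8, g = 0). Moved: (0.40 − 0.224)/1.20 − 0.224/0.80 = −0.13. Excluded: 0.40 − 0.28 = 0.12.

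**4. Between the ends, ρ = 0.5.** Ranges cover g from 0 to 1. Power is from simulated trials with 100 randomised per arm.

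| Moved | d, counted as early | Power | d, excluded |
|---|---|---|---|
| 5% | 0.28–0.30 | 49–55% | 0.35 |
| 10% | 0.19–0.22 | 25–35% | 0.30 |
| 20% | 0.04–0.11 | 5–10% | 0.22 |

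With no true effect and ρ = 0.5, the simulated chance of a significant result against early PTA rises from the nominal 2.5% to about 11%, 23% and 53% at 5%, 10% and 20% moved.

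**5. By randomised arm.** There is no selection bias, and type I error stays near 2.5% per side. If the crossover PTA brings the full effect (g = 1), the estimate is diluted:
- 10% crossover: d = 0.40 × 0.90 = 0.36, simulated power about 73%; 80% power needs 15.70/0.36² = 121.1, so 122 per group
- 20% crossover: d = 0.40 × 0.80 = 0.32, simulated power about 63%; 80% power needs 15.70/0.32² = 153.3, so 154 per group

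Here 15.70 = 2(1.960 + 0.842)². If the crossover PTA brings no gain, d stays at 0.40.

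**6. Direction.** Steps 2 to 4 need the change score to start at V0, so that a moved wound carries its early deterioration with it. The power statement refers to baseline to last visit, which supports this. The abstract, however, speaks of wound area changes after PTA, and the follow-up visits are timed from PTA. If the first value were taken at the PTA, a moved patient could start with a larger wound and have more absolute area to lose, which could push the bias the other way.

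**The case against.** The strongest reply is that the article nowhere plans an as-treated analysis. Early PTA and standard PTA may simply be arm labels: both arms receive PTA, and the elective arm is itself described as standard of care. In ordinary trial usage, crossover means a change in treatment received, not in analysis set. The references to treatment arm and treatment group fit that reading. A reader might infer from the crossover sentence that the sponsor intends to analyse by treatment received; the article does not support that, and the bias is conditional on the literal reading.

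A second reply is that analysis sets are commonly left to the full protocol or the SAP. That is also right, so the absence of an intention-to-treat statement is not the point here. What remains is text that is present: a stated change of group, in conflict with that group's 48 h definition, beside a comparison worded by PTA received.

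A reader might also say that the trigger is the primary endpoint itself. It is not. It is an undefined wound-healing complication, which can matter only before an elective PTA due within 6 weeks, while follow-up runs to 12 months. The two are correlated, not identical.

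Finally, the size rests on assumed rates and correlations, and clinicians would not select exactly the lowest-ranked patients. This is fair, and it is why a range is given. At 5% crossover and correlation 0.3 the loss is modest.

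**Conclusion.** The point holds in conditional form. The definition of the early arm, the crossover sentence and the wording of the primary comparison conflict. If they are followed literally, group membership depends on a correlate of the outcome. With change from V0, the comparison is then biased against early PTA: a true d of 0.40 becomes about 0.34 to −0.13 if the worst 5–20% are moved at correlation 0.3–0.8, and about 0.37 to 0.12 if they are excluded. The rate, the correlation and the gain from the crossover PTA are assumptions, and the direction could differ if change is measured from the PTA. It is not established that the trial will be analysed this way. Analysis by randomised arm removes the selection bias and leaves only dilution.

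**What to change.** - State that the primary and secondary analyses compare the randomised arms, whatever the timing of PTA received.
- Reword the crossover sentence so that an expedited PTA in the elective arm does not change arm membership, and reconcile it with the 48 h definition and with the wording of the primary comparison.
- Record the date and reason of each expedited PTA.
- Label any analysis by timing received as supplementary.
- Describe the stated 80% power as assuming no crossover.

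The clinical trigger is left as it stands.

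The text changes are small, but the statistical cost should be acknowledged. The estimate becomes that of the treatment strategy, diluted if the crossover PTA works. With full gain and 100 per group, power is about 73% at 10% crossover and 63% at 20%. Keeping 80% in those cases would take about 122 or 154 per group.

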**Fig. 1 Fig1:**
[figure not shown]
Timeline. The figure shows follow-up visits at respective time points during the study period. The specified times of the respective follow-up examinations refer to the time after the PTA. PTA = Percutaneous transluminal angioplasty, PAD = Peripheral arterial disease, T2D = Type 2 diabetes, DFU = Diabetic foot ulcer, RCT = Randomised controlled trial

The primary endpoint of the PTA-DFS Study is to assess the effect of early PTA on wound healing in T2D participants and chronic ischemic DFU. Wound healing is measured by the reduction of 3D wound area, assessed using clinical grading and 3D-camera analysis with AI-based evaluation of wound length, width, and depth. The secondary endpoint is the combined incidence of MALE and MACE post-angioplasty between early and elective PTA treatment, time to complete wound healing, major amputation rate and the need for new revascularization. Explanatory variables for the primary endpoint are differences in quantitative shifts in bacterial taxa with different oxygen requirements (aerobes, anaerobes) (Fig. 2). These shifts post-PTA will be analysed using appropriate statistical methods, such as Generalised Linear Mixed Models (GLMMs), accounting for treatment group (early PTA vs. elective PTA), bacterial taxa, and time, with random effects to adjust for individual variability. Another explanatory variable for wound healing is the change in oxygen saturation in the wound environment, measured by multispectral near-infrared spectroscopy (NIRS). These outcomes will be analysed using Cox proportional hazard models using time-to-event outcome for MALE/MACE events, adjusting for baseline covariates to evaluate the effectiveness of early PTA compared to standard treatment.

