One explanatory variable evaluates the effect of early PTA on wound microbiome dynamics. This objective aims to measure the beta-diversity changes of the wound microbiome, assessed via whole-genome sequencing and analysed using Bray–Curtis distances. In detail, taxonomic profiles from whole-genome sequencing of the wound microbiome will be generated using bioinformatics scripts. The sequencing data, produced via the Oxford Nanopore platform [36] will be analysed with Kraken2 [37] and minimap2 [38] based on a custom database including protozoan, fungal, and viral sequences. Visualisations for comparing metagenomic composition across taxonomic levels will be generated with custom scripts. Principal coordinate analysis based on Bray–Curtis distances will assess sample clustering, with the entire workflow provided as a reproducible Snakemake pipeline [39]. Effect sizes are based on expected changes in Bray–Curtis distances for beta-diversity. Nominal variables will be compared using the Chi-Square Test and Fisher's Exact Test where appropriate. Relationships between variables (e. g., changes in wound microbiome or local microcirculation and wound healing or complications) will be assessed using partial Pearson or Spearman correlation coefficients, with adjustments for confounders and multiple testing via the Bonferroni or Benjamini–Hochberg method. The standardised mean difference (Cohen's d) will be used for power analyses due to the lack of preliminary data on changes of ulcer area and combined incidence of MALE/MACE after early PTA. Changes in beta-diversity of the wound microbiome, will be analysed using Generalised Linear Mixed models with fixed effects including treatment group, bacterial taxa, time, and random effects to account for patient variability. Interaction terms will assess differential effects between treatment groups. The secondary endpoint includes combined MALE and MACE incidence post-angioplasty. Oxygen saturation in wound environment is measured as another explanatory outcome potentially linked to wound healing. Additional outcomes will include an evaluation of risk factors such as comorbidities (severity of anaemia and stages of chronic kidney disease), severity of insulin resistance, DSPN, the duration of hospital stay and interactions with medications, including antibiotics and antithrombotic therapies. Risk endpoints include the incidence of MALE, progression of diabetic complications (e.g., neuropathy), and hospital stay duration. These will be analysed using survival analysis methods and logistic regression to evaluate risk/benefit ratios. Multiplicity will be addressed as follows: The primary outcome will be analysed at a two-sided significance level of 0.05 without adjustment. For the prespecified family of confirmatory secondary outcomes, the family-wise error rate will be controlled at 0.05 using the Holm–Bonferroni procedure. For these outcomes, raw and adjusted p-values as well as corresponding adjusted 95% confidence intervals will be reported. Exploratory outcomes will not be adjusted for multiplicity and will be clearly identified as exploratory. Safety outcomes will be reported descriptively. The interaction effects of antibiotics, PTA timing, and concomitant antithrombotic treatments on both primary and secondary endpoints will be assessed using logistic regression models and subgroup analyses. Time-to-event clinical endpoints will be analysed with Kaplan–Meier survival curves, while covariate adjustments will be incorporated using Cox proportional hazards models. Correlation analyses (partial Pearson or Spearman coefficients) will account for confounders and include multiple comparison corrections via Bonferroni or Benjamini–Hochberg adjustments. Categorical variables will be compared using Chi-Square or Fisher's Exact Tests, while continuous variables will be analysed with Wilcoxon rank-sum tests or Student's t-tests, as appropriate. Two-tailed p-values below 0.05 will be considered statistically significant. Missing data will be summarised by variable, time point, and treatment arm, and patterns of missingness will be described graphically and statistically. The primary analysis will employ multiple imputation by chained equations (MICE; m = 20 imputations) under the assumption of missing at random (MAR). The imputation model will be specified to be congenial with the planned analysis and will include treatment arm, relevant baseline covariates (e. g., age, sex, ulcer duration, ulcer size, Wagner grade, HbA1c, infection status), and outcome variables. Continuous variables will be imputed using predictive mean matching, binary variables will be analysed via logistic regression, and ordinal variables will be analysed using proportional-odds models. Estimates will be combined using Rubin’s rules. Sensitivity analyses will include (i) complete-case analysis, (ii) best–worst and worst–best case scenarios, and (iii) a delta-adjusted pattern-mixture model to assess departures from MAR and exploring missing not at random (MNAR). All statistical analyses will be performed using the R Version 4.4 and SPSS for Windows 23.0 (SPSS Inc., Chicago, IL, USA). Figures are created with GraphPad Prism, Version 7.01 (GraphPad Software, Inc., La Jolla, CA, USA) or R, and Graphical abstracts using BioRender.com.

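### Visits V2–V6 and the MALE/MACE endpoint are timed from the PTA rather than from randomisation, and the starting point of the primary endpoint is contradictory

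*Protocol article*

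**What the plan says.** Table 1 places randomisation and a wound-area measurement at V0. Under Study design and randomisation protocol, the early arm has its PTA "within 48 h after leg artery stenosis (LAS) diagnosis", and the comparator is "the elective PTA group (standard of care with PTA within 6 weeks". The arms are otherwise to be treated alike.

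**Follow-up visits.** The same section states that "data will be collected at baseline recruitment (V0), during the index hospitalisation (V1; PTA and 24 h thereafter", and then "at follow-up visits at 1 (V2), 2 (V3), 3 (V4), 6 (V5), and 12 months (V6) post-PTA". The Fig. 1 legend confirms this: "The specified times of the respective follow-up examinations refer to the time after the PTA". The time row of Table 1 reads "Time Point 0 0 0 1 2 3 6 12". V0, the PTA and V1 thus all stand at time 0, and no visit falls within the wait. Both endpoints are marked for assessment from V1 onwards.

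**MALE/MACE.** Under Statistical methods and power calculation: "The secondary endpoint includes combined MALE and MACE incidence post-angioplasty". The Abstract (Methods) and the endpoint paragraph below Fig. 1 also place it after angioplasty, and the Abstract gives a 12-month window. The power paragraph, however, speaks of time to event running from baseline.

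**Primary endpoint.** In the Abstract, wound healing is "assessed by wound area changes after PTA using a 3D-camera". In the power paragraph it is the difference in wound area between the first and the last visit, without saying whether the first visit is V0 or V1.

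**Other secondary endpoints.** No origin is stated for time to complete healing, major amputation or new revascularisation.

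**The concern.** The trial asks whether a shorter wait for PTA helps. Any benefit arises partly or wholly during the weeks in which one arm has been treated and the other has not. A clock that starts at the PTA begins after those weeks in the elective arm.

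Three things are at stake:
- Limb and cardiac events during the wait are not part of an endpoint defined as post-angioplasty.
- Patients who die before the PTA, or have a major amputation before it, have no post-PTA time. The elective patients compared are those who came through the wait, so the comparison is no longer between the groups as randomised.
- Visits with the same label fall at different times since randomisation in the two arms.

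The crossover rule adds to this. An elective patient with wound-healing complications moves to immediate PTA, so the clock may start at a moment set by the patient's own course.

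**Working it through.** **1. The plan's own figure.** With d = 0.4, two-sided alpha 0.05 and 80% power, n per group = 2 × (1.960 + 0.842)² / 0.4² ≈ 98.1, rounded up to 99. The t-test version gives 99.08, rounded up to 100. Power at 100 per group is 80.4% (t-test). The stated 100 per group reproduces. The point concerns time zero, not this figure.

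**2. Follow-up from randomisation to V6.** Inputs are the 48 h and 6-week limits and V6 at 12 months after PTA. Assumption: diagnosis and randomisation coincide.
- Early arm: 2 + 365 = 367 days at most.
- Elective arm: 42 + 365 = 407 days at most.
- Difference: 40 days, or 40/367 = 10.9%.

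**3. MALE/MACE before the PTA clock starts.** The documents give no event rate. Assume a constant hazard and a 12-month risk p. The fraction with an event during a wait of w days is 1 − (1 − p)^(w/365).

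| 12-month risk p | 42-day wait, per 100 | Share of 12-month events | 21-day wait, per 100 | 2-day wait, per 100 |
|---|---|---|---|---|
| 20% | 2.5 | 12.7% | 1.3 | 0.1 |
| 30% | 4.0 | 13.4% | 2.0 | 0.2 |
| 40% | 5.7 | 14.3% | 2.9 | 0.3 |
| 50% | 7.7 | 15.3% | 3.9 | 0.4 |

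**4. What this does to a comparison.** Simulation, 2000 runs, 100 per arm, PTA at day 2 or day 42. Assume p = 30% and a hazard three times higher until the PTA.
- Mean events in 12 months from randomisation: 30.1 early, 35.6 elective.
- Mean events in 12 months from PTA: 29.7 early (99.4 patients reaching PTA event-free), 26.5 elective (88.3 reaching it).
- Risk among those reaching PTA: 29.7/99.4 = 29.9% and 26.5/88.3 = 30.0%. The true difference has vanished.
- Log-rank power in this setting is only 16% even from randomisation, and about 5% from PTA.

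**5. Healing, if early PTA does nothing but remove the wait.** Assume no healing before PTA, then exponential healing with a 26-week median in both arms. The early wait is taken as zero. Healed fraction = 1 − exp(−ln 2 × (t − wait)/26), with t in weeks from randomisation.
- 12 weeks: 27.4% early versus 14.8% elective with a 6-week wait, 12.6 points (6.0 points with a 3-week wait).
- 52 weeks: 75.0% versus 70.7%, 4.3 points (2.1 points with a 3-week wait).
- Counted from PTA: zero at every time.

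For time to healing with medians of 60, 90 and 120 days, simulated log-rank power from randomisation is 86%, 58% and 37%. From PTA it is 5%, 6% and 4%, which is the false-positive rate.

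**6. The two readings of the primary endpoint.** If the first measurement is at or after the PTA, as the Abstract and the Table 1 marks from V1 suggest, wound change during the wait is lost. If it is V0, as the power paragraph allows, the wait is included but the unequal follow-up of step 2 applies.

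**The case against.** A reader might infer that every visit and every outcome is timed from the PTA, so that the wait disappears from the whole trial. The text does not support that. V0 is at recruitment and includes wound area. The power paragraph uses the first visit and baseline as starting points, and on the visit numbering the first visit is V0. No origin is given for the other secondary endpoints. Outcome monitoring follows events over a 12-month period, with telephone contact for patients who cannot attend, and names no PTA start. No sentence expressly excludes events before PTA. The exclusion follows from the post-angioplasty definition, and the power paragraph contradicts that definition.

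Nor is the direction of bias settled. Lost waiting-time benefit, uncounted waiting events and longer elective follow-up all work against early PTA. Losing elective patients who heal before their PTA would work in its favour.

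The sizes also need care. The 12.6 points are for a healed fraction at 12 weeks, which is not a protocol endpoint. Near the last visit the same model gives 4.3 points. It also assumes no healing before PTA, although both arms receive standard care. The 42-day wait is a maximum, and no start is stated for the 6 weeks.

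These limits stand. They narrow the point but do not remove it: V2–V6 and the MALE/MACE definition still run from the PTA, and either reading of the primary endpoint leaves a defect.

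**Conclusion.** The point holds in this form: follow-up from V2 and the MALE/MACE endpoint start at the PTA, a post-randomisation event that allocation delays by up to 6 weeks in one arm, and the origin of the primary endpoint is contradictory. That the wait is lost from all outcomes is not established.

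The firmest figure is the follow-up difference of up to 40 days. It needs only the stated limits and the assumption that diagnosis and randomisation coincide. The 2.5–7.7 events per 100 elective patients rest on an assumed 12-month risk of 20–50%, a constant hazard and a full 6-week wait. The healing figures rest on an assumed 26-week median and on early PTA doing nothing but remove the wait. They show how large the loss could be, not what it will be. The contradiction needs resolving whatever the rates.

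**What to change.** - Make randomisation (V0) time zero for the primary and all secondary endpoints in both arms.
- Count every death, amputation, MALE and MACE from randomisation, including those before the elective PTA and in patients who never reach it.
- State that the allocated index PTA does not count as new revascularisation.
- Define the primary endpoint as wound-area change from V0 to a fixed time after randomisation. Either set the 12-month visit from randomisation in both arms, or keep the visits and model area on actual days since randomisation. The second route also serves patients already enrolled.
- Keep the PTA-timed visits for the explanatory NIRS and microbiome analyses. Moving all of V2–V6 to the randomisation clock would break their post-PTA spacing and could put the 1-month visit before an elective PTA.
- Reconcile the Abstract, the visit schedule with Table 1, the Fig. 1 legend with the endpoint paragraph below it, and Statistical methods and power calculation.

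The cost is an amendment of endpoint wording and, on the first route, of one visit window. The sample size is unchanged and no visits or staff are added. If the 12-month visit is moved, it falls up to 6 weeks sooner after the PTA in the elective arm, also for the samples taken then. The analysis must handle visit times that differ between arms.
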